## Abstract

In the past decades, we have witnessed tremendous developments in endovascular surgery. Nowadays, highly complex procedures are performed by minimally invasive means. A key point is equipment improvement. Modern C-arms provide advanced imaging capabilities, facilitating endovascular navigation with an adequate open surgical environment. Nevertheless, radiation exposure remains an issue of concern. This study aims to analyze radiation used during endovascular procedures according to complexity, comparing a mobile X-ray system with a hybrid room (fixed X-ray system). This is an observational and prospective study based on a cohort of non-randomized patients treated by endovascular procedures in a Vascular Surgery department using two imaging systems. The study is planned for a 3-year duration with a recruitment period of 30 months (beginning 20 July 2021) and a 1-month follow-up period for each patient. This is the first prospective study designed to describe the radiation dose according to the complexity of the procedure. Another strength of this study is that radiologic variables are obtained directly from the C-arm and no additional measurements are required for feasibility benefit. The results from this study will help us determine the level of radiation in different endovascular procedures, in view of their complexity.

## 1. Introduction

Treating patients with vascular pathology has experienced a revolution in recent years with the growth of endovascular procedures. This evolution is related to the advent of novel therapeutic tools (such as pressure balloons, drug balloons, stents, and endograft) and the advancement of X-ray technology.

We can perform this type of treatment using surgical X-ray equipment (also called C-arms). The term C-arm refers to equipment composed of a high-tension generator and a tube that produces X-rays, which penetrate the patient’s body, and converts these rays into a visible image [1].

Modern C-arms provide high-quality radiological images in real-time, enabling the execution of highly complex procedures that would be unthinkable with older equipment [2,3].

To perform these procedures in a sterile environment, we can use mobile C-arms in a standard operating room or fixed equipment in a so-called hybrid operating room, which combines the features of an operating room with a radiology room.

Nevertheless, radiation exposure and its potentially harmful effects on patients and healthcare professionals remain an issue of concern [2,3,4,5].

Increased exposure to ionizing radiation could lead to deterministic and stochastic injuries with immediate, intermediate, or long-term onset because of the increased number of diagnostic and therapeutic procedures performed on patients [1,2,3,4,5,6].

Deterministic effects (“tissue reactions”) are biological effects that occur as a result from the death of a large number of cells in a tissue or organ. They usually appear after a specific dose (threshold dose or threshold of clinical effects), being more severe the higher the amount received [1,4,5,6]. Skin lesions and lens opacities are examples of deterministic effects after radiation exposure [7,8,9,10].

Stochastic or probabilistic effects occur by chance, and their likelihood, but not severity, increases with increasing dose. There is no threshold dose, and effects can occur at low doses. The development of malignancy is the most common stochastic effect of radiation exposure [7,8,9,10]. Stochastic effects often appear years after exposure.

The decision to use a fixed C-arm or a mobile C-arm in our facility is made based on the availability of the X-ray equipment and the schedule of the procedures. In this study, we focus on arterial procedures: endovascular treatment of thoracic, abdominal, and thoracoabdominal aortic aneurysms, and procedures involving the revascularization of lower limbs.

Notwithstanding the widespread use of X-ray imaging units, there are a lack of published data about the impact of radiation exposure, and fixed C-arms are still related to higher radiation exposure [11,12,13].

The collection and subsequent analysis of radiological, clinical, and procedural parameters would identify opportunities for improvement in workflow and biosafety.

The results of this study may act as a springboard for further research on the comparison of radiation exposure between both X-ray equipment types according to complexity stratification of endovascular procedures. The identification of procedures that involve higher doses of radiation will allow the development of strategies to enhance safety in operating rooms where radiation exposure is involved.

## 2. Aims and Objectives

### 2.1. Primary Objective

This study aims to analyze radiation used during endovascular procedures according to complexity, comparing a mobile X-ray system (Philips Zenition 70 ^®^) with a hybrid room (Philips Azurion ^®^).

### 2.2. Secondary Objectives

The secondary objectives are: (1) Define the diagnostic reference radiation doses (DRLs) according to the procedure and its complexity, following the guidelines of the International Commission of Radiation Protection (ICRP) [14,15,16,17,18,19] and the European Council Directive 2013/59/EURATOM [20]. (2) Compare the dosimetric information provided in the dose reports of each procedure, based on the degree of complexity, in view of the implemented radiation protection measures. (3) Analyze the contrast dose used during the procedures on each device. (4) Associate the radiation dose of endovascular procedures with patients’ body mass index.

## 3. Methods

### 3.1. Study Design

This observational and prospective study is based on a cohort of non-randomized patients treated by endovascular procedures in a Vascular Surgery department.

### 3.2. Setting

The study is planned for 3-year duration with a recruitment period of 30 months and a 1-month follow-up period for each patient.

Patients will be recruited in outpatient consultations and hospitalization when the endovascular procedure is indicated according to standard clinical practice.

### 3.3. Participants

All patients who are candidates for an endovascular procedure will be invited to take part in the study. Oral and written information will be given.

### 3.4. Inclusion Criteria

All patients of ≥18 years agree to participate in the study by signing informed consent for one of the following procedures: (a) elective endovascular procedures for exclusion of thoracic and/or abdominal aortic aneurysm; (b) elective endovascular procedures for lower limb-threatening ischemia.

### 3.5. Exclusion Criteria

Diagnostic arteriography and/or verification arteriography procedures;Endovascular procedures of upper limbs;Endovascular venous procedures.

### 3.6. Outcome Measures

Peak skin dose (PSD) is the primary outcome of this study. PSD is defined as the maximum absorbed dose to skin from exposure to X-rays [20]. Secondary outcomes are described in Table 1 [2,3,4,5,6,7].

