### 5.2. Statistical Analysis

We will perform a general descriptive analysis of the study variables. The results will be expressed as means and standard deviation, median, maximum, and minimum value, range and third quartile for the quantitative variables and for the categorical variables, the absolute and relative frequencies of each category. All study variables will be described, and descriptive statistics will be used according to the nature of the variable.

The principal analysis is the peak skin dose and other radiation dose variables described in Table 1. It will be analyzed by indirect radiological parameters, such as KAP or PSD. The secondary research will include:− The study population will be described according to the baseline characteristics and the type of procedure.− The procedure performed according to X-ray device used (mobile vs. fixed) and the level of complexity of the procedure will be described.− Partnership studies will be carried out.

Estimators will be accompanied by a 95% confidence interval. Statistical significance has been set at a probability level of <0.05.

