## Figures and Tables

**Table 1 mps-06-00049-t001:** Description of other radiation dose measures.

Parameters	Description
**Air kerma (AK)**	Represents the kinetic energy released per unit mass when an X-ray beam travels through air. The unit is milliGrays (mGy). It will be recorded by the system.
**Air-kerma area product (KAP or dose area product, DAP)**	The KAP is the product of two factors, namely the air kerma free in the air over the area of the X-ray beam in a plane perpendicular to the beam axis.
**Fluoroscopy time (FT)**	The time of exposure to X-ray, expressed in seconds. Fluoroscopy is a radiographic technique used for the visualization of anatomical structures in motion that allows guiding different diagnostic and therapeutic procedures in real-time. The unit is seconds. It will be recorded by the system.
**Contrast volume**	The total volume of contrast injected into the patient during the procedure. The unit is milliliter (mL).
**Body mass index (BMI)**	The measure of the weight compared to the height. The total amount of dose delivered will be correlated with patient size and weight.
**Number of DSA series**	The total number of digital subtraction series.
**Procedure time**	The total time interval from the start and end of the procedures, recorded in minutes (min).
**Type of anesthesia**	Described as general or loco-regional.

**Table 2 mps-06-00049-t002:** List of endovascular procedures.

Endovascular Procedures	Description
(1) Endovascular exclusion of abdominal aortic aneurysm	Placement of stent graft for internal lining of the aorta to exclude abdominal aneurysm.
(2) Endovascular exclusion of thoracic aorta	Placement of stent graft for internal lining of the thoracic aorta to exclude aneurysm, dissection, intramural hematoma, penetrating aortic ulcer or traumatic aortic injury.
(3) Endovascular exclusion of thoracoabdominal aortic aneurysm	Placement of stent graft for internal lining of the aorta to exclude thoraco-abdominal aneurysm.
(4) Endoleaks repair	Procedures that involve repairing blood flow between the graft and the aneurysm.
(5) Iliac percutaneous transluminal angioplasty or recanalization	Flow restoration procedure of the iliac sector through dilation with balloon catheter, with or without stent placement.
(6) Iliac stent	Stent placement in the iliac sector.
(7) Femoropopliteal percutaneous transluminal angioplasty or recanalization	Flow restoration procedure of femoropopliteal sector with or without stent placement.

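### BMI is listed as a secondary outcome but used as a predictor of dose; class it as a patient characteristic and adjust the device comparison of peak skin dose for it

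*Protocol article*

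**What the plan says.** Section 3.6 of the protocol article fixes the outcomes: "Peak skin dose (PSD) is the primary outcome of this study", and then "Secondary outcomes are described in Table 1". No row of the table is exempted.

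Table 1 carries the title "Description of other radiation dose measures" and has eight rows, two of which are BMI and type of anesthesia. The BMI row reads "The measure of the weight compared to the height. The total amount of dose delivered will be correlated with patient size and weight". The anesthesia row says only "Described as general or loco-regional".

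Secondary objective 4 (section 2.2) is "Associate the radiation dose of endovascular procedures with patients’ body mass index". Section 5.2 adds "The principal analysis is the peak skin dose and other radiation dose variables described in Table 1". It plans a description by X-ray device and complexity level and mentions association analyses without detail. It names no covariate and rules none out.

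**The concern.** A secondary outcome is something the study measures as a result. BMI is fixed before the patient enters either room, so the imaging system cannot change it. Its scientific use here is as an explanatory variable for dose, which is how objective 4 and its own table row describe it. One variable therefore has two roles that do not fit together.

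The role matters because of the primary objective, which is to compare the mobile C-arm with the hybrid room according to complexity (section 2.1). The cohort is not randomised, and the room depends on availability and schedule (sections 1, 3.1 and 4). The complexity levels (section 3.8.3 and Table 3) are built from access, anatomy, recanalization, device placement and complications. Body size is not among them, so stratifying by complexity does not deal with BMI. If BMI differed systematically between rooms, part of that difference would appear as a device effect on dose. Even without such a difference, the dose variation that BMI explains stays in the residual and widens the promised 95% confidence intervals.

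**Working it through.** **Step 1. The passages side by side**

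| Place | Role given to BMI |
|---|---|
| Section 3.6, pointing to Table 1 | secondary outcome |
| Table 1, BMI row ("The total amount of dose delivered will be correlated with patient size and weight") | variable that dose is related to |
| Section 2.2, objective 4 | variable that dose is related to |
| Section 5.2, description by device and complexity | not stated |

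The first row conflicts with the second and third. Objective 4 does not mention type of anesthesia, so for that variable there is only a misplaced label and no contradiction. The plan has no figure of its own to reproduce on this point.

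**Step 2. Inputs for the size**

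- From the documents: 150 to 200 procedures a year (section 5.1) and 30 months of recruitment (section 3.2), giving 150 × 2.5 = 375 to 200 × 2.5 = 500 procedures.
- Assumed, because the documents give none of these: SD of log peak skin dose 0.8; SD of BMI 5 kg/m²; equal use of the two rooms; three equal complexity levels, hence m = 375/3 = 125 to 500/3 ≈ 167 procedures per level; and R², the share of log-dose variance within device and level that BMI explains, of 0.05, 0.10 or 0.25.

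**Step 3. Gain in precision**

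On the log scale, adjustment multiplies the interval width by about √(1 − R²). The equivalent gain in sample size is 1/(1 − R²). Neither depends on the SDs or on m.

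| R² | √(1 − R²) | Interval narrower by | 1/(1 − R²) |
|---|---|---|---|
| 0.05 | 0.975 | 2.5% | 1.05 |
| 0.10 | 0.949 | 5.1% | 1.11 |
| 0.25 | 0.866 | 13.4% | 1.33 |

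This ignores the one degree of freedom spent on the slope and the small loss of precision when BMI differs between rooms.

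**Step 4. What a systematic difference would do**

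The slope of log dose on BMI is √R² × 0.8/5. For each 1 kg/m² of true mean difference between rooms, the unadjusted dose ratio is multiplied by exp(slope):

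- R² = 0.05: exp(0.224 × 0.16) = exp(0.036) = 1.036
- R² = 0.10: exp(0.316 × 0.16) = exp(0.051) = 1.052
- R² = 0.25: exp(0.5 × 0.16) = exp(0.08) = 1.083

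The documents do not show that such a difference exists or how large it might be.

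**Step 5. Chance imbalance is not a further harm**

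At m = 125, the 95% limit of a chance BMI difference is 1.96 × 5 × √(4/125) = 1.75 kg/m². At R² = 0.10 this shifts log dose by 0.0506 × 1.75 = 0.089, a ratio of 1.093. The unadjusted half-width is 1.96 × 0.8 × √(4/125) = 0.28, and √0.10 × 0.28 = 0.316 × 0.28 = 0.089, the same number. In general, log shift = √R² × unadjusted half-width. The unadjusted interval already contains this variation, so it must not be added to the precision loss in Step 3.

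**The case against.** The strongest reply is that only the pointer in section 3.6 is loose. Wherever the article describes how BMI will be used, it relates dose to BMI. Section 5.2 restricts the principal analysis to radiation dose variables from Table 1, which does not naturally cover BMI or anesthesia. Contrast volume, procedure time and the number of DSA series are not radiation doses either, so the table reads as a general variable list under a loose title. A covariate list is commonly left to a full protocol or statistical analysis plan, neither of which is shown.

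Much of this stands. A reader might infer from the outcome label that BMI is kept out of the device comparison, or that it will be tested between devices as an outcome. The documents support neither reading: no passage says so, and an outcome label does not bar a variable from a model. The absence of a covariate list is not the finding. Nor do the documents link room assignment to BMI, so a systematic imbalance is possible but not shown.

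Two things remain. Section 3.6 as written gives BMI a role that objective 4 contradicts, and a separate analysis plan would not correct that text. And adjusting the device comparison for a baseline variable that the protocol itself expects to be related to dose is a better method than stratifying by complexity alone.

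**Conclusion.** The inconsistency in BMI's role is real. Relabelling alone would be clerical. What makes the point worth acting on is that an adjusted device comparison is available at almost no cost. The quantified gain is an interval narrower by about 2.5%, 5% or 13% if BMI explains 5%, 10% or 25% of log-dose variance: modest at the lower values and useful at the highest. These shares are assumptions. The second benefit is protection against a systematic BMI difference between rooms, whose size cannot be derived from the documents. For type of anesthesia the point is no more than a tidy-up of its label.

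**What to change.** - **Section 3.6 and Table 1:** take BMI and type of anesthesia out of the secondary outcomes and list them as patient or procedure characteristics. Describe them by device without testing them as outcomes.
- **Section 5.2:** state that the device-by-complexity comparison of log peak skin dose includes BMI as a continuous covariate.

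The cost is a few words in three places and one model term. No new data are needed, because BMI is already among the recorded variables.

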### 3.7. Data Collection

The main source of information is the patient’s medical history and anamnesis. Radiological dose reports will be collected directly from the devices, including the main radiation dose metrics.

### 3.8. Data Variables

#### 3.8.1. Imaging Systems

The X-ray device used on each procedure will be described as a dichotomous variable: Mobile C-arm (MCA) or hybrid room (HR). The MCA equipment is Zenition 70^®^ (Philips, The Netherlands) with a 30 × 30 cm flat-panel detector. The C-arm is color-coded and fully balanced with ability to angulate from +90 to −50° [21].

Philips Azurion 7^®^ is the X-ray equipment in a HR with a 20” flat detector and equipped with a workstation for image processing and fusion imaging (VesselNavigator, Phillips Healthcare, Best, The Netherlands). All compatible applications in the interventional lab via the central touch screen module and FlexVision Pro [22].

#### 3.8.2. Endovascular Procedures

The type of procedures (Table 2), arterial approaches, and contrast volume will all be recorded [23,24].

#### 3.8.3. Complexity Levels

To obtain a reliable comparison across endovascular procedures, we have devised a framework for categorizing procedures on three levels of complexity considering type of surgery. In aortic procedures, the degree of complexity depends on arterial access, aortic neck anatomy, contralateral leg catheterization and iliac anatomy. For peripheral artery procedures we consider the Global Limb Anatomic Staging System (GLASS) (infrainguinal chronic limb threatening ischemia) [24], the Trans-Atlantic Inter-Society Consensus Document on Management of Peripheral Arterial Disease classification (TASC II) (aortoiliac lesion) [25], the possibility of recanalization, and the occurrence of dissection and/or thrombosis (Table 3).

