## 4. Study Procedures

Identify patients with scheduled endovascular procedures.Once the patient is scheduled for endovascular surgery, we will explain the study and request their participation. If the patient agrees to participate, they will sign an informed consent document.The procedure will be scheduled either in the hybrid room or in the conventional room with a mobile C-arm, according to their availability.Collect information about medical history and anthropometric data during the interview and from the medical records in a database.The scheduled endovascular procedure will be carried out according to standard clinical practice.Obtain radiation dose parameters extracted directly from Philips Azurion^®^ and Philips Zenition 70^®^.If the endovascular procedure exceeds the radiation dose threshold (DAP ≥ 500 Gy·cm^2^, PSD ≥ 2000 mGy or AK ≥ 2000 mGy), the coordinating researcher will receive an alarm and will perform a patient clinical evaluation looking for any warning symptoms or signs.
In case of not finding signs of radiodermatitis, the patient will be informed of the warning signs, we will provide an information sheet, and preferential outpatient check-ups will be scheduled.In case of presenting clinical signs of radiodermatitis, the patient will be evaluated by a dermatologist.Based on standard clinical practice, patients will be assessed at one month.

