## 10. Conclusions

In conclusion, the analysis of radiation data of endovascular procedures is essential to detect which imaging systems and procedures involve higher doses. This is an observational and prospective study that attempts to examine the radiation dosage in two distinct imaging systems, using a classification of complexity levels in order to achieve a reliable comparison.

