**High Complexity**
A. Angioplasty/stent of any territory
1. Difficult arterial puncture requiring a change to open approach or arterialficult arterial puncture requiring a change to open approach or arterial access 2. Access from upper limb (UL) 3. Laborious recanalization of the stenosis/occlusion requiring one of the following conditions: guidewire/catheter changes collaboration of a second vascular surgeon retrograde puncture 4. Final angiogram with dissection/thrombosis requiring extra procedures (for example thrombectomy) 5. Presence of complications of arterial access
B. Recanalization of any territory
1. Difficult puncture requiring a change of approach point/open approach 2. Access from UL 3. Recanalization of an entire arterial axis (iliac, femoral and/or distal trunks)—TASC C/D (aorto-iliac), GLASS 3. 4. Laborious recanalization of the stenosis/occlusion requiring one of the following conditions: guidewire/catheter changes collaboration of a second vascular surgeon retrograde puncture 5. Final angiogram with dissection/thrombosis requiring extra procedures (for example thrombectomy) 6. Presence of complications of arterial access 7. Despite multiple attempts, it is not possible to recanalize the occlusion
C. Aortic endoprosthesis
1. Complication of the arterial access (open or percutaneous) 2. Hostile anatomy (neck length < 15 mm and/or neck diameter > 32 mm, length of iliac arteries < 15 mm and/or diameter > 20 mm) 3. Complex catheterization of the contralateral limb requiring extra procedures (for example, single-loop snare) 4. Additional procedures for endoleak treatment (such as central cuff extension or additional iliac limb) 5. Additional procedures as embolization of inferior mesenteric/internal iliac artery, placement of endo-anchor, etc. 6. Chimney or snorkel technique 7. Fenestrated or branched aortic endograft 8. Iliac branch

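### Table 3 grades complexity partly from events that follow room assignment and that the imaging system may influence, so device contrasts within its levels do not estimate the device effect

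*Protocol article*

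**What the plan says.** Section 2.1 sets the primary objective: to "analyze radiation used during endovascular procedures according to complexity, comparing a mobile X-ray system" with a hybrid room. Section 3.6 names the outcome: "Peak skin dose (PSD) is the primary outcome of this study". Section 4 sets the allocation: "The procedure will be scheduled either in the hybrid room or in the conventional room with a mobile C-arm, according to their availability". The device is therefore fixed before the procedure begins.

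Section 3.8.3 describes the grade. For aortic work, "the degree of complexity depends on arterial access, aortic neck anatomy, contralateral leg catheterization and iliac anatomy". For peripheral work it uses GLASS and TASC II together with "the possibility of recanalization, and the occurrence of dissection and/or thrombosis (Table 3"). Table 3 turns this into Low, Medium and High levels. One High criterion for recanalization is "Despite multiple attempts, it is not possible to recanalize the occlusion".

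The Conclusions tie the grade to the two imaging systems, "using a classification of complexity levels in order to achieve a reliable comparison". Section 3.8.1 describes the hybrid room as "equipped with a workstation for image processing and fusion imaging" and mentions no such tool for the mobile C-arm. The article defines no separate grade from pre-procedural information.

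**The concern.** Rooms are not randomised, and the grade is the protocol's stated means of making the comparison reliable. A stratifier used for that purpose should be fixed before the exposure acts. Here part of it is a record of how the case went on the device being evaluated.

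Two problems follow if the device influences those events. First, if one system really makes navigation easier, some hard cases move to a lower level. Part of the dose saving then shows up as a change in case mix between levels and is lost from the within-level contrast. Second, if a system changes only what is seen or how a case is scored (for example, by showing more dissections or endoleaks), cases of different underlying difficulty are compared at the same level, and a difference can appear when none exists. At stake is the interpretation of the primary comparison of peak skin dose between devices.

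**Working it through.** **Step 1. When each Table 3 criterion becomes known.**

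| Block | Known only during the procedure or at its end | Known or plannable beforehand |
|---|---|---|
| Low, angioplasty | All 4: puncture, guide passage, final angiogram, access complications | None |
| Medium, aortic | 4 of 5: approach, implantation, contralateral limb, final endoleak | Neck and iliac anatomy |
| High, recanalization | 5 of 7: change of approach, laborious passage, final dissection/thrombosis, access complications, failure | TASC/GLASS extent; upper-limb access, if planned |
| High, aortic | Access complication, complex contralateral catheterization, endoleak procedures | Hostile anatomy, chimney, fenestrated/branched graft, iliac branch |

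The grade is a mixture, and a large part of it follows room assignment.

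**Step 2. Is there a route from device to grade?** Fusion imaging is described for the hybrid room only (section 3.8.1). The abstract says that the imaging of modern C-arms helps navigation; it says this of such equipment in general. Several criteria score navigation. The route is plausible, but the protocol gives no figure for it.

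**Step 3. Illustration.** The protocol has no figure to reproduce; its 150 to 200 procedures a year is a volume forecast. All coefficients below are assumptions.

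- Difficulty U ~ N(0, 1); device assigned at random.
- log dose = 0.6 × U + noise with SD 0.7; no direct device term.
- Grade score = U + noise with SD 0.5, cut at the mobile-arm tertiles.
- *Relabelling*: the hybrid room lowers the score by 0.5 SD; U and dose are unchanged.
- *Real easing*: the hybrid room lowers U itself by 0.5 SD, and so also dose. The overall ratio is exp(−0.6 × 0.5) = exp(−0.30) = 0.74.

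Hybrid/mobile geometric mean dose ratios:

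| Scenario | Overall | Low | Medium | High |
|---|---|---|---|---|
| Device changes nothing | 1.00 | 1.00 | 1.00 | 1.00 |
| Real easing, 0.5 SD | 0.74 | 0.87 | 0.93 | 0.89 |
| Relabelling, 30% of cases can be regraded | 1.00 | 1.07 | 1.07 | 1.04 |
| Relabelling, all cases can be regraded | 1.00 | 1.18 | 1.25 | 1.20 |
| Relabelling upwards by 0.25 SD, all cases | 1.00 | 0.92 | 0.89 | 0.92 |

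Under real easing, the share of the log effect left within levels is ln 0.87 / ln 0.74 = 0.46 (Low), ln 0.93 / ln 0.74 = 0.24 (Medium) and ln 0.89 / ln 0.74 = 0.39 (High).

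**Step 4. A second model, with grading events modelled directly.** Here log dose = 0.5 × U + c × event + noise with SD 0.6. A case is High if its anatomy is hard or an event occurs, and the hybrid room changes the odds of an event.

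- Event odds ratio 1: every ratio is 1.00.
- c = 0 (no device effect on dose), odds ratio 0.7 to 0.3: spurious ratios of 1.02 to 1.06 in the lower level and 1.03 to 1.08 in High.
- c = 0.5, odds ratio 0.5: overall 0.94, but 1.04 in the lower level and 0.97 in High. The lower level holds only event-free cases, so a saving from avoided events cannot show there. High holds 52% of mobile and 44% of hybrid cases.
- Strata from pre-procedural anatomy alone: 1.00 when c = 0; 0.95 and 0.93 for c = 0.5 and odds ratio 0.5, close to the overall 0.94.

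**The case against.** **Much of the grade is fixed beforehand.** TASC II, GLASS, neck and iliac dimensions and planned graft type do not depend on the room, and a case with a High anatomical or planned-graft criterion should be High in either. This stands, and it is why the figure for full regrading is an upper illustration.

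**Part of the aim is descriptive.** Reference levels by procedure and complexity are a secondary objective, and section 5.2 says only that procedures will be described by device and level. Realised complexity is a sensible basis for describing dose. This stands too. But section 2.1 and the Conclusions also attach the grade to the comparison of the two systems.

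**No stratified model is fixed.** Section 5.2 names none. An analysis plan that is not shown could adjust for pre-procedural factors, and nothing prevents an overall device comparison. This lowers the severity. It does not remove the point, because the grading rule and the claim of reliability are both stated in the article.

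**A stronger reading does not hold.** A reader might infer that a system that eases catheterization will look worse within every level, with a false excess of about 18% to 25%. Those figures need the device to change the grade while leaving real difficulty and dose untouched, with every case open to regrading. The protocol describes no such pure relabelling. When the easing is real, the first model gives attenuation with the right sign in every level; the second gives a reversal in the lower level only.

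**Conclusion.** The structural point holds. The room is set at scheduling, Table 3 then grades partly on what happens in that room, and the primary objective compares devices by that grade. Contrasts within levels therefore do not estimate the device effect unless the device leaves all the grading events unchanged, in which case there is no bias.

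Size and direction cannot be derived from the protocol. Under the assumed coefficients, a real benefit of 0.74 shrinks to between 0.87 and 0.93, and a pure grading effect creates a ratio of about 1.04 to 1.07 with 30% of cases open to regrading, or up to about 1.25 with all of them. The shift, the share and the dose coefficients are all assumptions. The unbiased overall ratios also rest on random assignment in the simulation, whereas the study assigns by availability.

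This is a should-fix. It does not show that the study will find a false device difference, and it does not undermine the use of Table 3 to describe dose.

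**What to change.** For the device comparison, define a second grade that uses only information available before the procedure: territory, TASC II or GLASS stage, neck and iliac dimensions, planned graft technique and planned access. Stratify or adjust by that grade, and report the overall device comparison alongside it. Keep the Table 3 level for describing dose and for diagnostic reference levels, and label device results by Table 3 level as secondary. Tabulating the share of cases at each Table 3 level by device would also show whether the realised grade differs between rooms.

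The cost is protocol wording and one derived variable. Table 3 already needs most of the inputs, though whether access or technique was planned may require one extra recorded field. The pre-procedural grade will explain less of the variation in dose than the realised one, so device estimates adjusted for it will be somewhat less precise.
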